#### Chance2Act Health Intervention

The Chance2Act digital health intervention is a web-based behavior modification program based on the 4 main constructs of the TTM. This model uses the stages of change to integrate the principles and processes of behavior change. The stages of change are influenced by the processes of change (activities people use to progress through stages), decisional balance (an individual’s relative weighing of the pros and cons of changing), and self-efficacy (situation-specific confidence that people can cope with without relapsing to their former behavior) [21]. This intervention emphasizes the role of the immediate family members in creating a healthy social environment favoring weight loss. The main components of the intervention will be identified from an extensive review of published studies, health education materials, and gray literature that can boost the readiness to change for weight loss. This is the first version of the study protocol.

#### Delivery of the Chance2Act Intervention

The Chance2Act intervention will be delivered to the individual participants by the investigators. Participants will be given the Chance2Act website using their login account and password. Access to the website is free of charge. The intervention will comprise 4 main modules and will be delivered in sequence. Each module will take approximately 2 weeks to be completed. The sequence of the intervention was developed based on the Process of Change construct of the TTM [21].

The baseline measurements will be taken before the initiation of the intervention. Follow-up will be done by the investigator after the completion of the first 2 modules, approximately at week 5, and after the completion of the whole package of the intervention, at week 9. In addition, participants can seek help from the investigators to navigate through the functions of the Chance2Act website through the built-in messaging system.

The Chance2Act is a tailored intervention whereby the participants will receive personalized coaching about their weight-related behavioral problems to boost their motivation via the built-in messaging system. The principal investigator will actively monitor the progress of each participant and intervene according to the health education module. Information will be given through text on the website, sets of infographics, animations, and videos. Health quizzes will be conducted to assess the comprehensibility of the module. They will be given printed materials such as weight loss checklists and dietary and exercise weekly plan templates to assist their weight loss journey. Each participant will have at least 1 adult family member to join as part of the intervention modules. The family members will be guided on the ideal way to fully support the participants’ efforts for weight loss. They will receive clear information on their role during the weight loss journey.

Participants are expected to finish each module in 2 weeks and give the required feedback and responses at the end of the module accordingly. Follow-up will be done by the investigators. Participants who did not comply with the follow-up requirements will be considered a loss to follow-up. Data analysis will be by the intention-to-treat (ITT). There is no specific concomitant care and intervention that are permitted or prohibited during the trial.

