### Phase 2: Nonrandomized Controlled Trial

#### Study Setting

Phase 2 of the study will be conducted as a nonrandomized controlled trial, which is aimed to determine the effectiveness of the Chance2Act intervention. The study is expected to be conducted over 4 to 6 months, at 2 government health clinics in Pahang state, Malaysia. These 2 health clinics will be enrolled by the researcher and are expected to have similarities in terms of the sociodemographic background of the local community. The assignment into either the intervention or control group will be based on the health clinic where the participants are getting their treatment from. One health clinic will be assigned as the intervention arm whereas another clinic as the control arm. The study flowchart for phase 2 is summarized in Figure 2. This is an unblinded study with a parallel assignment (ie, intervention vs control [usual care] with an allocation ratio of 1:1). Blinding is not possible due to the nature of the intervention which is mainly health education.

To avoid contamination, the 2 health clinics will not be selected from neighboring localities. Access to the Chance2Act website will be restricted only to the registered participants and family members from the intervention arm. A username and password will be provided to log in to the website. The participants, family members, and the medical staff at the participating health clinics are not allowed to share any intervention material with a third party.

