#### Study Population

The target population is patients with T2D aged 20-60 years old, with a BMI of more or equal to 23 kg/m^2^, who are not ready to act for weight loss. Study participants will be selected via purposive sampling method to ensure homogeneity between the 2 arms.

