#### Participants Recruitment

The patients with T2D, who come for a routine appointment at the selected health clinics during the recruitment period will be approached, given the Patient Information Sheet (PIS) about the study, and invited to participate. If they are willing to participate, they will be screened by the investigators to determine their eligibility based on the inclusion and exclusion criteria. Then, written informed consent will be obtained from those who are eligible. Participants from the intervention arm will be given a username and password to access the Chance2Act intervention, whereas participants from the control arm will continue the existing health education module in the health clinic.

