#### Eligibility Criteria

The patients with T2D aged 20 to 65 years old who fulfill all the following inclusion criteria will be included (1) BMI of more or equal to 23kg/m^2^; (2) in the precontemplation, contemplation, or preparation stage of change based on the s-weight questionnaire [19]; (3) able to understand, read, and write in the Malay language; (4) have access to any electronic device with internet service; (5) able to understand information and perform tasks in the digital environment, especially website; and (6) have at least 1 adult family member who is living in the same household.

Patients who fulfill any of the following criteria will be excluded (1) patients who are pregnant; (2) patients with advanced comorbidity and mental conditions that will affect participation and understanding of the study protocol, for example, vision problem, physically unfit to stand up and walk, advanced heart failure or cancer, and schizophrenia; and (3) patients who die or are transferred out to other health clinics during the study period.

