#### Study Outcome

Outcome measures are categorized into primary and secondary outcomes. These measures will be obtained from both the intervention and control arm at baseline, fifth week, and ninth week after the initiation of the intervention.

The primary outcome will be measured by the changes of the stages of change using the Malay version of the S-weight questionnaire. The secondary outcomes will be measured by (1) a change in dietary self-efficacy will be measured by the WEL-Q, (2) a change in exercise self-efficacy will be measured by the SEE, (3) a change in decisional balance for weight loss will be measured by the DBI, (4) change in family support for diet and exercise will be measured by the social support scale for diet and exercise, (5) change in BMI, (6) change in waist circumference, and (7) change in body fat percentage.

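### The intervention expects a relative to join, but eligibility in both clinics asks only for a co-resident one, so the intervention arm can be enriched for willing families

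*Protocol article*

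**What the plan says.** Under Eligibility Criteria, one list serves both clinics, and its family criterion is that the patient "have at least 1 adult family member who is living in the same household". Whether that relative is willing to take part is not asked.

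Under Delivery of the Chance2Act Intervention, the expectation is stronger: "Each participant will have at least 1 adult family member to join as part of the intervention modules". Under Study Setting, relatives have a role in one arm only: "Access to the Chance2Act website will be restricted only to the registered participants and family members from the intervention arm". The Control Group section describes usual care with no family component, and an offer of the intervention once T2 data are collected.

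On how people enter the arms:

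- Study Setting: "The assignment into either the intervention or control group will be based on the health clinic where the participants are getting their treatment from", with one clinic per arm, and "This is an unblinded study with a parallel assignment".
- Study Population: "Study participants will be selected via purposive sampling method to ensure homogeneity between the 2 arms".
- Participants Recruitment: patients attending routine appointments "will be approached, given the Patient Information Sheet (PIS) about the study, and invited to participate". Screening and written consent come afterwards.

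Under Study Outcome, family support is itself a secondary outcome: "change in family support for diet and exercise will be measured by the social support scale for diet and exercise". It is measured in both arms at baseline, week 5 and week 9. Under Data Management and Statistical Analysis, the homogeneity check is confined to demographic characteristics, and the effectiveness analysis is intention-to-treat with GEE.

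**The concern.** The written entry criterion is the same in both clinics, but what taking part demands is not. At the intervention clinic a patient whose relatives will not join has a reason to decline, and an unblinded recruiter sampling purposively has a reason to prefer someone else. At the control clinic neither reason applies, or at most it is deferred to the later offer. The same criterion could therefore yield different populations in the two arms.

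The difference would not be neutral. The Introduction presents family support as helping people progress, and the Chance2Act Health Intervention section gives immediate family an emphasized role. On the protocol's own theory, then, a willing relative is prognostic for the primary outcome and closely related to one secondary outcome. Selection at entry would favour the intervention on readiness to change, and it cannot be undone once recruitment has closed.

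**Working it through.** The plan gives no figure on this point, so there is none to reproduce. The check compares the sections and then bounds the possible bias.

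**Comparison of sections**

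| Step | Intervention clinic | Control clinic |
|---|---|---|
| Family criterion at entry | co-resident adult relative | same |
| Relative expected to take part during the trial | yes, at least one | no |
| Arm knowable when first approached | yes (arm follows from clinic, unblinded) | yes |
| Relative's agreement stated as a condition of consent | no | no |
| Family support measured at baseline | yes | yes |
| Family support named in the homogeneity check | no | no |

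The rows on entry and participation show the mismatch. The row on consent shows that the text does not turn the delivery expectation into an entry condition. The last two rows show that data to detect an imbalance will exist, but that the stated check does not name them.

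**Bound on the bias in the primary outcome.** The documents give none of these inputs, so all are assumptions:

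- w: share of otherwise eligible patients with no willing relative
- a, b: usual-care probability of reaching the action stage with and without a willing relative
- f: fraction of patients without a willing relative who are lost at the intervention clinic only

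With no intervention effect, the expected control rate is (1−w)a + wb. The expected intervention rate is [(1−w)a + w(1−f)b] / (1−wf). The difference is

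(a−b) × (1−w)wf / (1−wf).

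At f = 0 this is 0. It rises with f, and at f = 1 it is w(a−b), the ceiling.

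Ceiling values:

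- a = 0.30, b = 0.15: w = 0.20 gives 0.20 × 0.15 = 0.03; w = 0.40 gives 0.40 × 0.15 = 0.06.
- a = 0.40, b = 0.20: w = 0.20 gives 0.20 × 0.20 = 0.04; w = 0.40 gives 0.40 × 0.20 = 0.08.
- Wider range: w = 0.10 with a gap of 0.10 gives 0.01; w = 0.50 with a gap of 0.30 gives 0.15.

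**Consequence for the test.** Take 62 per arm (Abstract), an assumed control rate of 20% and a simple two-sided 5% comparison of two proportions with no attrition. A spurious difference would be significant in the intervention's favour about 10% of the time at 5 points, 25% at 10 points and 46% at 15 points. The nominal rate in that direction is 2.5%.

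**The case against.** The strongest reply is that the sentence on relatives joining stands under Delivery and describes a component of the intervention, not a gate. Eligibility is common to both clinics, consent is taken from whoever meets it, and intention-to-treat keeps an enrolled participant whose relative never joins. The information sheet is not shown. It may describe the family component identically in both clinics, particularly as controls are later offered the intervention. This stands, and it means that enrichment is a possibility and not a stated feature of the design. It does not remove the possibility: intention-to-treat acts only after enrolment, and even an identical sheet leaves the immediate demand on relatives in one arm only.

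A second reply is that perceived family support is measured at baseline in both arms, so an imbalance could be seen. That also stands. The gap is narrower: the stated check covers demographics and does not name this score.

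Third, the secondary outcome is change in family support. A higher starting level does not by itself inflate change and may leave less room to improve. A reader might infer that family support would be biased even more strongly than readiness, but the documents do not support that, even as to direction.

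Finally, the fix is imperfect. A control relative's promise to take part after T2 is not the same commitment as joining now, and asking for it may prompt some support in the control arm. Both are fair costs, and both are small.

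**Conclusion.** The point holds as an avoidable asymmetry that can select different patients into the two arms. A reader might infer that the intervention clinic will in fact be enriched. The documents do not support that: nothing makes a relative's agreement a condition of entry, and nothing excludes a participant whose relative stays out.

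The size is unknown. It is zero if nobody declines, is passed over or is lost for want of a relative. The ceiling is w(a−b), reached only if every such patient is lost at the intervention clinic and none at the control clinic. On the assumed inputs of 20% to 40% without a willing relative and rates of 30% against 15%, the ceiling is 3 to 6 points. That is modest beside the 30-point difference used under Sample Size Calculation, so this is a worthwhile low-cost improvement and not a fatal flaw. Clinic-level, non-randomized allocation already limits inference, and this is one directional route within it that can be narrowed.

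**What to change.** 1. In both clinics, reword the sixth inclusion criterion as: *at least 1 adult household family member who agrees, before baseline, to take part in the Chance2Act family modules when access is given*. For controls, access means the offer made after T2 data collection.
2. Use one common information sheet, describing both arms, in both clinics.
3. Add the baseline family-support scores for diet and exercise to the between-arm comparison, and include them as covariates in the GEE models. This helps only so far as the scores capture willingness to join, so it supplements steps 1 and 2 and does not replace them.

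Withholding the arm until the baseline questionnaires are complete is optional and not essential.

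Cost: a change to one criterion and to the information sheet, with notice to the ethics committees. There would be somewhat fewer eligible controls, possibly slight prompting of control families, and results that apply to patients with a willing relative, which the intervention already presumes. The Results section expected data collection to begin in June 2023. If recruitment has closed, only step 3 is still available, and the possible selection should be stated as a limitation.

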#### Data Collection

For both arms, the data for phase 2 will be obtained from a set case report form (CRF) which consists of demographic data, self-administered questionnaires, anthropometric measurements, and disease profiles. At week 0 (T0), once consented, anthropometric measurements will be taken by the investigator and clinical data will be obtained from the medical records.

Clear written and verbal instructions will be given on how to answer the questionnaires. Participants will be requested to circle which options suit them the most. Participants will be allowed to answer the questionnaires while waiting their turn for medical consultation. They will be encouraged to seek clarification from investigators at any time, should any queries arise.

Before the initiation of the study, all investigators will be trained regarding the study procedures to minimize variability and bias during the data collection. The study procedures will comply with the Malaysian Guideline for Good Clinical Practice, fourth edition [22].

#### Study Instruments

For the anthropometric measurement, the height will be taken using a wall mounted stadiometer (SECA 206) and recorded to the nearest 0.1 cm. The body weight and body fat composition (total fat percentage and visceral fat percentage) will be measured using a body fat composition monitor (Omron HBF-222T) with an accuracy of 0.1 kg and 0.1%, respectively. Waist circumference will be measured to the nearest 0.2 cm using nonstretchable measuring tape midway between the lower margin of the 12th rib and the top of the iliac crest, just above the umbilicus in a horizontal plane.

The set of self-administered questionnaires will consist of (1) a Stages of Change (SOC) questionnaire using the S-weight; (2) a Weight-efficacy Lifestyle Questionnaire (WEL-Q); (3) Self-efficacy for Exercise (SEE); (4) a Decisional Balance Inventory (DBI) for weight loss; and (5) social support scale for diet and exercise. Verbal instruction will be given on how to complete the questionnaire. On average, participants will be expected to spend approximately 30 minutes to complete the questionnaires. Once they have finished, they will submit the questionnaires to the investigator to ensure the completeness of the responses given.

The S-weight questionnaire was initially developed in English and Spanish language simultaneously [19,23]. This questionnaire has been translated into Malay language and tested among the adolescent obese population [24]. It consists of a brief series of self-report questions assessing weight loss intentions and current activities. The S-weight has 5 mutually exclusive items each representing the 5 stages of change: precontemplation, contemplation, preparation, action, and maintenance. S-weight has been reported as an efficient tool to assess the readiness to change in weight management by a review [25].

A validated Malay version of WEL-Q will be used to assess dietary self-efficacy for weight loss. It is used to measure an individual’s confidence to control eating in specific circumstances. It consists of 20 items representing 5 subscales which are negative emotions, availability, social pressure, physical discomfort, and positive activities. WEL-Q uses a Likert scale ranging from 0 (not confident) to 9 (very confident). The total score of each subscale is ranged between 0 and 36. The higher score shows better control to resist eating. WEL-Q has been tested among the Malaysian population with T2D. It is reported to have a good internal consistency reliability with Cronbach α of .893. Construct validity was measured by the item total correlation of *r*>0.700 and *P*<.01, and interitem correlation of *r*<0.005 and *P*<.01 [26].

The SEE was originally developed by Bandura and has been modified to suit the Malaysian population. It consists of 18 items measuring an individual’s confidence to maintain routine exercises. A 5-point Likert scale is used ranging from 1 (cannot do) to 5 (certain can do). The Malay version of SEE has been tested among Malaysian patients with T2D with a composite reliability (CR) of 0.921 [27].

The DBI was developed in the English language by O’Connell and Velicer in 1988 [28]. It measures an individual’s belief of the perceived pros and cons of weight loss. It consists of 20 Likert scale items, 10 items for pro (even-numbered items) and 10 items for cons (odd-numbered items). The scale ranges from 1 (not important at all) to 5 (very important). The total score range is 10 to 50. The Malay version of DBI shows good reliability. For the pro scale reliability was reported as Cronbach α=.902, intraclass correlation (ICC) (95% CI) is 0.88 (0.86-0.90). The con scale Cronbach α=.739 and ICC (95% CI) is 0.72 (0.70-0.78) [24].

The social support scale for diet and exercise was developed in the English language in 1987 [29]. In this study, the social support for diet and exercise will be measured separately and used specifically to measure the perceived social support received from the family members. The social support scale for diet consists of 10 items. Items 1-5 measure the encouragement, whereas items 6-10 measure discouragement received from the family members. The social support scale for exercise behavior consists of 12 items. The measurement uses a Likert scale ranging from 1 (never) to 5 (very often). A higher score implies that the participants have better social support received from their family members to lose weight. These questionnaires have been translated into Malay language and validated. This questionnaire has been proven valid and reliable. The social support for diet has internal consistency reliability of Cronbach α of .61-.91 and test-retest reliability, *r* of 0.55-0.86 [29]. The social support scale for exercise was reported to be reliable for the Malaysian population. It was reported to have a CR of 0.918, an average variance extracted of 0.560, and an ICC (based on test-retest) of 0.920 [30].

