### Data Management and Statistical Analysis

For phase 1, the data will be entered in Microsoft Excel (Microsoft Office 365) and ready for analysis. The content validity will be assessed by the experts’ ratings. The CVI will be assessed based on 2 indices, the Item-level Content Validity Index (I-CVI) and Scale-level Content Validity Index (S-CVI). The criteria that will be assessed are mainly content relevance. The I-CVI will reflect each item or intervention activity relevancy, whereas S-CVI will reflect the overall module relevancy. Then, the face validation will be determined based on the FVI. Similarly, the FVI will be assessed based on 2 indices, the Item-level Face Validity Index (I-FVI) and the Scale-level Face Validity Index (S-FVI). The criteria that will be evaluated are the module clarity, simplicity, and ambiguity. For both CVI and FVI, the results of at least 0.83 will be considered acceptable [31,32].

For phase 2, the data will be entered into IBM SPSS Statistics (version 27; IBM Corp). Each CRF will be given a unique identifier. Screening for missing, redundant data or wrong coding will be done. The investigator will try to contact the participants to complete the missing data via telephone. Then, any remaining missing data will be dealt with an appropriate missing data handling method. For redundant data, only 1 data will be selected. The wrongly coded data will be corrected accordingly based on the CRF. Then, the data will be ready for analysis.

For the descriptive statistics, the normality tests will be used to determine the distribution of the data. The normally distributed will be described by using mean and SD, whereas not normally distributed data will be described by using the median and IQR. The categorical data will be presented by using frequency and percentage.

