### Ethical Considerations

This study has been approved by the Medical Research and Ethics Committee, Ministry of Health Malaysia (NMRR ID-22-01073-4YT IIR) and Universiti Teknologi MARA Research Ethics Committee (REC/07/2022PG/MR/157). The ethics committees will be informed in case of any changes to the study protocol. Before participants’ enrollment, PIS will be given and explained to all the participants. Written informed consent will be obtained once patients understand the study well. The research assistants will be trained to conduct these procedures. The risk of privacy breaches is minimal. The website will only contain health education material. None of the personal information and medical information will be uploaded on the website. The data for the outcome measures will be stored by the investigator in a password-protected computer and cloud account provided by the Ministry of Health Malaysia (MyGovucUC 2.0 account). The data will be destroyed after 3 years postcompletion of the study. The permission to use the questionnaires has been obtained from the authors with proper citation.

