### Strengths and Limitations

To our best knowledge, the Chance2Act intervention is the first web-based intervention that promotes behavior change, specifically designed for adults with T2D with obesity but not yet prepared to start losing weight. Developing an intervention for this population group is crucial, as a significant number (59%-79%) of them are not yet actively making weight loss efforts [7,8]. We hope that this intervention can contribute to better outcomes of obesity care in patients with T2D, thus, potentially leading to the metabolic benefits associated with weight loss.

In terms of the study design, the selection of a nonrandomized controlled trial method is acceptable due to the nature of the intervention given. Since the health interventions are delivered through a website, blinding of the study participants and researcher is not possible. The participants need to be aware of group assignments, thereby they will access the website and be involved in the intervention.

Another potential limitation that may arise during the study is that participants who do manifest interest are limited to patients with T2D with good digital literacy skills only. As a result, the findings of the study may not be applicable to a broader population, especially those with limited digital literacy. Digital literacy of the study participants may influence the conclusions concerning the uptake and attrition rate of the intervention.

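### The unblinded investigator role both coaches the intervention arm and handles the self-reported primary outcome, which can bias the readiness comparison toward the intervention

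*Protocol article*

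**What the plan says.** **Intervention.** The protocol article, under Delivery of the Chance2Act Intervention, states: "The Chance2Act intervention will be delivered to the individual participants by the investigators". The same section describes personalised coaching by message to raise motivation, and adds: "The principal investigator will actively monitor the progress of each participant and intervene according to the health education module". Follow-up at about week 5 and at week 9 is also done by the investigator.

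**Outcome.** Under Study Outcome, the primary outcome is change of stage on the Malay S-weight. Study Instruments describes this as a self-report tool with five mutually exclusive items, one per stage. It is collected at baseline, week 5 and week 9 in both arms.

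**Handling of the answers.**
- Data Collection, on participants completing the forms: "They will be encouraged to seek clarification from investigators at any time, should any queries arise".
- Study Instruments, on finishing: "they will submit the questionnaires to the investigator to ensure the completeness of the responses given".
- Data Management and Statistical Analysis: "The investigator will try to contact the participants to complete the missing data via telephone".

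**Blinding and safeguards.** Study Setting: "This is an unblinded study with a parallel assignment". Strengths and Limitations, referring to delivery through a website: "blinding of the study participants and researcher is not possible". The safeguards stated are that questionnaires are self-administered and that all investigators are trained to limit variability and bias in data collection.

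**The concern.** A participant coached for about eight weeks toward starting weight loss is asked, at the end, to say whether they have started. The answer goes to the role that did the coaching. Saying that one has reached the action stage is the answer that pleases. Control participants also hand their forms to an investigator, but the protocol describes no coaching tie between them. Their usual care comes from clinic staff such as diabetes educators and dieticians.

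The week-5 and week-9 comparisons could therefore mix real change with reporting to please, in one arm only. Recruiting more participants would not remove this. A fixed distortion becomes more likely to reach significance as the sample grows. The self-efficacy, decisional balance and family support scales follow the same route and share the exposure.

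The protocol's account of blinding explains why participants must know their arm. It does not explain why the role that motivates them should also clarify, receive and complete their answers.

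**Working it through.** **Step 1: who does what.**

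| Task | Role named | Section |
|---|---|---|
| Deliver intervention | investigators | Delivery of the Chance2Act Intervention |
| Monitor progress and intervene | principal investigator | same |
| Follow-up at weeks 5 and 9 | the investigator | same |
| Clarify questionnaire items | investigators | Data Collection |
| Receive forms, check completeness | the investigator | Study Instruments |
| Telephone for missing data | the investigator | Data Management and Statistical Analysis |

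One role covers every row, and no section divides it. The telephone step concerns missing phase 2 data in general, which includes S-weight but is not specific to it.

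**Step 2: the plan's own figure.** Sample Size Calculation gives 44 per arm for a 30-point difference, alpha .05, 80% power. The Kelsey formula is n = (z₀.₉₇₅ + z₀.₈₀)² × 2p̄(1−p̄)/d². The control proportion is not stated. Assuming 35% against 65%, p̄ = 0.50, so n = (1.960 + 0.842)² × 2 × 0.25/0.09 = 7.85 × 0.50/0.09 = 43.6, which rounds up to 44. Control proportions from 30% to 40% also give 44, so 35% is a reasonable value for the illustration. The present point does not change this figure.

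**Step 3: what differential over-reporting would do (assumption only).** Suppose there is no true effect, a proportion p = 0.35 of controls is at action, and a share q of intervention participants who are not ready report action. The observed intervention proportion is p₁ = p + (1−p)q.
- q = 0.10: p₁ = 0.35 + 0.65 × 0.10 = 0.415, a spurious 6.5 points.
- q = 0.20: p₁ = 0.35 + 0.65 × 0.20 = 0.480, a spurious 13 points.

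A two-sided two-proportion normal test stands in for the planned GEE. Let d = p₁ − p, SE₀ = √[2p̄(1−p̄)/n] and SE₁ = √{[p(1−p) + p₁(1−p₁)]/n}. The chance of a significant result favouring the intervention is Φ[(d − 1.96·SE₀)/SE₁]. The opposite tail adds at most 0.005.

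| n per arm | q | SE₀ | SE₁ | (d − 1.96·SE₀)/SE₁ | Two-sided rejection |
|---|---|---|---|---|---|
| 44 | 0.10 | 0.1036 | 0.1034 | −1.34 | 9.6% |
| 44 | 0.20 | 0.1050 | 0.1041 | −0.73 | 23% |
| 62 | 0.10 | 0.0873 | 0.0871 | −1.22 | 11.5% |
| 62 | 0.20 | 0.0885 | 0.0877 | −0.50 | 31% |

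The 44 is the stated minimum and the 62 is the per-arm number in the Abstract. Sample Size Calculation gives 65 recruited per arm, which would move the result slightly upward from the 62 rows. The nominal rate is 5%. The document gives no value for q, so these results show only how sensitive the comparison is. They do not estimate the bias in this trial.

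**The case against.** **The same person?** A reader might infer that one individual both coaches and collects. The text does not say so. It names the principal investigator as the one who monitors and intervenes, speaks elsewhere of investigators in the plural, and has two clinics. A fuller protocol may assign the tasks by name. This stands, and the point is limited to the role: what the article states puts both tasks on it and does not divide them.

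**Is bias certain?** No. S-weight is self-administered, the stated purpose of the hand-in is completeness, and investigators are trained. A completeness check on receipt should also leave few S-weight blanks to telephone about. These safeguards lessen the risk. They do not remove a participant's wish to please a coach, and the open invitation to ask for clarification weakens self-administration. The direction is plausible, but the size is unknown.

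**Can it be avoided altogether?** No. Participants know their arm and report their own stage, with a family member involved. Separating the tasks reaches only the part that comes through the collector, and not all of q in the illustration would belong to that part.

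**Are neutral staff at hand?** Ethical Considerations says "The research assistants will be trained to conduct these procedures", which might suggest so. The procedures meant there are the information sheet and consent. The assistants' number, location and independence from coaching are not given. Private completion does not rest on them.

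**Could measured weight expose over-reporting?** It is tempting to compare declared action with measured weight loss. S-weight asks about intentions and current activities, and a participant truly in action may not have lost weight by week 5 or 9. The comparison cannot separate over-reporting from real change.

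**Conclusion.** The concern holds in a limited form. The article gives one unblinded investigator role both the motivational coaching of the intervention arm and the clarifying, receipt, checking and telephone completion of a self-reported primary outcome. The stated reason for not blinding does not cover this overlap. It can bias the readiness comparison toward the intervention.

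The size cannot be derived from the document. With no true effect, 35% of controls at action and an assumed 10-20% over-reporting, false-positive rates would be about 10-23% at 44 per arm and 12-31% at 62. These figures rest wholly on the assumed rate, and the remedy would remove only the collector-related share.

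The change should be made because it protects the primary outcome, costs little, and cannot be replaced by an analysis afterwards.

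**What to change.** 1. At T1 and T2, in both clinics, have S-weight and the other scales completed privately. Use either an online form with required fields or paper returned in a sealed envelope bearing only the study ID. Nobody who coaches checks completeness. Eligibility already requires an internet device and the ability to work on a website, although this alone does not prove that online completion will be practical; paper remains the alternative.
2. Handle queries and telephone completion in both clinics from a fixed neutral script, by existing team members who do not coach where these are available. Record the mode of completion, and add a sensitivity analysis without telephone-completed S-weight answers.
3. Keep T1 and T2 S-weight answers from the coaching investigators until T2 is complete. This cannot extend to baseline, because investigators screen for eligibility and the S-weight stage is an inclusion criterion.
4. State as a limitation that self-report bias remains because participants know their arm.

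The cost is one form or envelope procedure, a short script, an extra data field and one sensitivity analysis. Participants would get slightly less help with unclear items, and paper may yield a few more blanks.
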